**Fig. 2 Fig2:**
[figure not shown]
Using cellular phenotypes to identify likely lithium-responsive genes. To reduce the number of comparisons and preserve statistical power, iPSC-derived neurons will be used to identify a smaller number of genes likely to be involved in lithium’s action. iPSC-derived neurons from lithium responders and non-responders will be treated both with and without lithium. RNAseq will be conducted and genes sought whose expression changes in responders but not non-responders. These genes will comprise a limited number of a priori hypotheses for initial testing

The gene expression data will also be used to develop gene expression networks that can then be compared between the four conditions. It is likely that, more than specific genes, it is changes in the functional modules or groups of genes that are most robustly changed in response to lithium. Such a network-based approach may also be more informative regarding the biology that is altered by lithium and different in responders.

### Genotyping and genetic data

Genotyping will be completed using PsychChip, which was developed on an Illumina platform for the Psychiatric Genomics Consortium (PGC). This chip includes the 50,000 most significant SNPs from several psychiatric disorders, as well as 250 K SNPs exome and framework GWAS content. We will use PLINK (http://pngu.mgh.harvard.edu/purcell/plink/) to evaluate and clean the genetic data received from TGen for 1) genotypic completeness, 2) average SNP heterozygosity, and 3) average genotyping quality score. For each SNP we will review 1) genotypic completeness, 2) average SNP heterozygosity, 3) average genotypic quality score, 4) minor allele frequency (MAF), and 5) p-values for tests of deviation from Hardy-Weinberg equilibrium. After generating a filtered dataset, we will examine Q-Q plots of association statistics with case-control status defined by good versus poor responders in order to look for systematic deviations from expectation that may further reflect artefacts in the data. Through these procedures, we will generate a final, cleaned dataset for the downstream analyses. Notable findings will all be reviewed in further detail as a final quality control check to confirm that they are not due to artefacts of low MAF, low genotyping completeness, batch or laboratory effects, or population stratification. In addition, we will visually examine the actual intensity plots of the individual best SNPs to confirm the quality of the genotype calls and ensure there is no evidence of systematic error that might lead to spurious results.

### Statistics

For the analysis of the Prospective Study, we will examine the outcome for lithium response as a time to event, where the event is defined as clinical relapse as defined above. For this we will use Cox Proportional Hazards models of the form:$$ \log\ \mathrm{h}\left(\mathrm{t}\right) = \upalpha \left(\mathrm{t}\right) + {\upbeta}_1{\mathrm{X}}_1 + \dots + {\upbeta}_{\mathrm{k}}{\mathrm{X}}_{\mathrm{k}} $$

where h(t) is the hazard of relapse at time (t) and the time axis is defined as the time from stabilization on drug to either clinical relapse, censoring due to loss to follow-up or discontinuation of study medication, or the end of the follow-up period. This model is semi-parametric in that the baseline hazard of relapse can take any form, but the covariates enter the model linearly and are assumed to have constant relative hazard over the entire time period. This assumption of constant relative hazard over time can be evaluated (and remedied if needed) by including in the model interactions terms between the covariate of interest and time. Building on this framework, we will test in separate models whether the SNPs identified in the ConLIGen Retrospective Study are significantly associated with the relative hazard of clinical relapse. We will include in the models covariates for age, sex, clinical site, and up to 10 quantitative indices of ancestry (if preliminary analyses of the genetic data suggest evidence of population stratification in the sample) to control for the potential confounding effects on these associations. We will also be able to include a covariate for an indicator variable capturing whether the patient entered the prospective study already on lithium as allowed by the protocol in order to control for this as well as to test whether associations differ for these versus other patients.

We will also examine repeated quantitative measures of depressive or manic symptoms taken at regular intervals over the period of follow-up. This will address the number of symptoms subjects continued to suffer even when they were considered in remission. For the repeated measures analyses, we will use longitudinal data methods to associate SNPs with differences in symptom measures over time. In particular, we will use linear regression models with general estimating equations (GEE) to account for the correlation engendered by repeated measures on the same participants. We will explore the repeated measures data to diagnose the nature of this correlation and then treat it as a nuisance variable in the model. We will then test whether the SNPs identified in the Retrospective Study or other retrospective datasets (ConLiGen) are significantly associated with differences in mean scores on the measures of depressive or manic symptoms, controlling for time of assessment, age, sex, clinical site, and the same quantitative indices of ancestry as the in the Cox model if deemed necessary. We will further explore for possible interactions between the SNP and time to test whether the effect of the SNP on depressive or manic symptoms changes over time.

To determine whether the effects of SNPs found to be associated with response in these analyses are specific to lithium treatment, we will use two strategies. First, in the time to event and repeated measures analyses described above, we will examine whether the inclusion of a covariate describing prior disease episode frequency affects the estimated association between SNPs and clinical relapse and/or symptom differences. If the estimated association is mitigated, this will suggest that the SNPs are associated with the natural course of disease in general. If, however, the estimated association persists, this will suggest that the association is specific to lithium responsiveness. To further confirm this possibility, we will examine the data from the Depakote arm of the Prospective Study. We will test whether the identified SNPs predict clinical relapse or symptom differences among patients who are crossed over to Depakote. If they are not associated, this will suggest the variants are associated specifically with lithium responsiveness.

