### Participants

Inclusion Criteria: 1) Any phase of bipolar I disorder, including depressive, manic, hypomanic, mixed, or baseline/euthymic/not symptomatic; 2) LNPs and IPLTs(as meant?) will be required to have had at least one affective episode in the last 12 months meeting DSM-IV criteria, but CLTPs will be exempted from this criterion if they present without any history of mood episodes meeting DSM-IV criteria in the last 6 months; 3) both outpatients and inpatients will be permitted to enroll into this study; 4) they must be able to give informed consent, in the judgment of the investigator; 5) age greater than or equal to 18 years; 6) women of child-bearing potential agree to inform their doctor at the earliest possible time of their plans to conceive, to use adequate contraception (e.g. oral contraceptives, intrauterine device, barrier methods, or total abstinence from intercourse), and to understand the risks of lithium to the fetus and infant. Depo Provera is acceptable if it is started 3 months prior to enrollment; 7) currently symptomatic, as defined as a CGI-S-BP-Overall of greater than or equal to 3 (mild severity), unless the patient enters the study already stable on lithium monotherapy.

Exclusion Criteria: 1) Unwilling or unable to comply with study requirements; 2) renal impairment (serum creatinine >1.5 mg/dL); 3) thyroid stimulating hormone (TSH) level over >20 % above the upper normal limit (participants maintained on thyroid medication must be euthyroid for at least 3 months before Visit 1; 4) other contraindications to lithium, as will be defined in the medication manual; 5) currently in crisis such that inpatient hospitalization or other crisis management should take priority; 6) although we have not excluded all subjects meeting criteria for alcohol/drug dependence, those meeting criteria for physical dependence requiring acute detoxification from alcohol dependence, opiate dependence or barbiturate dependence will be excluded; 7) pregnant or breastfeeding; 8) women of child-bearing potential who aren’t able to agree to the requirements specified above; 9) those who have participated in a clinical trial of an investigational drug within the past 1 month; 10) history of lithium toxicity, not due to mismanagement or overdose that required treatment.

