### Physical and laboratory monitoring

During the baseline period, vital signs and weight will be recorded. In addition, an EKG will be required for participants over the age of 40 as clinically indicated. The EKG requirement will be waived if an EKG had been obtained within 3 months of the baseline visit and a report is available. Laboratory assessments of BUN, creatinine, electrolytes, TSH and a urine pregnancy test (if applicable) will be obtained at baseline and will be repeated based on APA guidelines for recommended lithium monitoring (see Tables 1 and 2). Drug screens will not be routinely administered; however, administration of drug screening as part of ongoing treatment is at the discretion of the treating physician at any time, after consultation with the participant.

**Table 1 Tab1:** Lab monitoring schedule

	Baseline	Stabilization		O^a^	M^b^
Test	Baseline	2 weeks	12 weeks	16 weeks	Every 6 months during 24 months of additional follow-up
Vitals/Weight	X		X		X
EKG^c^	X if age > 40				
BUN	X		X		X
Creatinine	X		X		X
Pregnancy	X				
TSH	X		X		X
CBC	X				
Electrolytes	X		X		X
Lithium	X	X	X	X	X
Genetics Samples	X				

^a^Observation phase

^b^Maintenance phase

^c^If clinically indicated, as determined by the study physician

**Table 2 Tab2:** Assessment schedule (time in weeks)

	B	Stabilization						O	Maintenance
	-1	0	4	8	12	14	16	Q 2 wks × 8 wks then monthly visits	Cross over to Valproic Acid for mood episode on lithium
CGI-S-BP by doctor	X	X	X	X	X	X	X	X	X
Mood episode checklist	X	X	X	X	X	X	X	X	X
Consent	X								
MINI- PLUS	X								
Demographics/course of illness	X								
HAM-A		X			X		X		X
MADRS		X	X		X		X	X	X
QIDS-SR 16	X	X	X	X	X	X	X	X	X
YMRS/CARS – M		X	X		X			X	X
Side Effects Survey	X	X	X	X	X	X	X	X	X
Q-LES-Q	X				X		X		X
IRS	X				X		X		X
MSSI	X	X	X		X		X		X
Serious Adverse Event Form	X	X	X	X	X		X	X	X

*O* observation phase, *B* baseline, *ET* Early Termination, *Mini-PLUS* Extended Mini-International Neuropsychiatric Interview, *MADRS* Montgomery Asberg Depression Rating Scale, *QIDS-SR 16* Quick Inventory of Depressive Symptomatology Self-Report, *YMRS* Young Mania Rating Scale, *CARS-M*: Clinician Administered Rating Scale for Mania, *HAM-A* Hamilton Anxiety Rating Scale, *CGI-BP* Clinical Global Impressions of Severity - Bipolar Version, *Q-LES-Q* quality of life, enjoyment, and satisfaction questionnaire, *IRS* impulsivity rating scale, *MSSI* The Modified Scale of Suicidal Ideation

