### Symptom severity

Clinical Global Impressions of Severity Scale-Bipolar Version (CGI-BP) [44]. The CGI-BP is a modified version of the original CGI designed specifically for use in assessing global illness severity and/or change in patients with bipolar disorder; it assesses overall bipolar illness, depression, and mania. While the original CGI has been criticized for lack of reliability, the CGI-BP has been shown to have excellent inter-rater reliability. Not surprisingly, placebo response rates have been shown to be lower with the CGI-BP, compared to the HAM-D or MADRS in bipolar disorder. In contrast to symptom-severity scales, the CGI-BP is an integrated measure of illness severity that permits the incorporation of an assessment of function at work, social, family settings, etc. In contrast to the MADRS and HAM-D, it is not encumbered by the inability to distinguish improved somatic function (appetite and sleep) from medication-induced adverse events, which is important when studying medications that cause weight gain or somnolence.Montgomery Asberg Depression Rating Scale (MADRS) [45]. A 10-item clinician-rated measure of depression will be used to examine the extent of each patient’s current depressive symptoms.Young Mania Rating Scale (YMRS) [46]. An 11-item, clinician-rated measure that queries symptoms of mania.Clinician Administered Rating Scale for Mania (CARS-M) [47]. The CARS-M is a reliable and valid 15-item, clinician-rated measure of mania The CARS-M incorporates a number of methodological improvements in comparison to more frequently utilized mania rating scales, such as the YMRS. For example, the CARS-M separately assesses the presence of psychotic symptoms (e.g., delusions and hallucinations). Given the overlap in symptoms assessed on the YMRS and CARS-M, an integrated version will be developed and utilized for the current study, minimizing patient burden, yet allowing full-scale scores to be derived for each measure.Quick Inventory of Depressive Symptomatology Self-Report (QIDS-SR16) [48]. A 16-item self-report measure of depressive symptoms.

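### The secondary symptom-score models omit starting severity and entry route, so a SNP for symptom severity could pass the plan's first lithium-specificity check

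*Protocol article*

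**What the plan says.** All references are to the protocol article.

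- **Outcome.** The Statistics section analyses "repeated quantitative measures of depressive or manic symptoms taken at regular intervals over the period of follow-up" by linear regression with GEE and asks whether SNPs are "significantly associated with differences in mean scores on the measures of depressive or manic symptoms". The outcome is a level, not a change from a starting value.
- **Covariates.** The models are fitted "controlling for time of assessment, age, sex, clinical site, and the same quantitative indices of ancestry as the in the Cox model", the ancestry indices only if deemed necessary. Of the Cox model's optional terms, only the ancestry indices are carried over. The indicator for entering already on lithium is offered in the Cox paragraph and not repeated here.
- **Specificity checks.** The first adds "a covariate describing prior disease episode frequency" to both the Cox and the repeated-measures models. If the SNP association persists, it is taken as a sign of lithium specificity. The second tests the same SNPs for relapse or symptom differences in patients crossed over to Depakote. A SNP-by-time interaction is to be explored.
- **Available scores.** Table 2 (Physical and laboratory monitoring) marks MADRS, YMRS/CARS-M and QIDS-SR 16 at week 0.
- **Who enters.** Participants admits any mood phase and requires a CGI-S-BP Overall of at least 3, "unless the patient enters the study already stable on lithium monotherapy".

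**The concern.** A patient's mean score during follow-up reflects both how ill that patient tends to be and how well lithium works. The models separate these only through demographics, site, ancestry and, in the check, episode frequency. How often episodes occur and how severe symptoms are when measured are different traits. A SNP linked to the second but not the first would leave its estimate unchanged when episode frequency is added, and the plan's rule would then call it lithium-specific.

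This matters because there is no placebo arm. The Discussion itself names separating gene effects from natural course as a central design problem and relies on covariate adjustment to deal with it. A lesser cost is that any part of the follow-up score predictable from the starting score stays in the residual and widens the standard error of every SNP effect.

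**Working it through.** **The plan's own figure.** The only stated power is about 80 % for a hazard ratio of 1.4 with 700 patients, for the Cox model (Power section and the Fig. 3 caption). A Schoenfeld calculation (two-sided 0.05, dominant model, 50 % wild-type relapse, no dropout) gives 83 % for HR 1.4 and 78 % for 1/1.4 at an allele frequency of 0.15, so the figure can be reproduced. The text gives no allele frequency, so the match is conditional. It does not bear on the GEE models, for which no power is stated; 80 % is used below only as an assumed starting point.

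**Precision.** Let ρ be the correlation between the week-0 score and a patient's mean follow-up score (assumed; not in the documents). Adjusting multiplies the residual variance by 1 − ρ². A two-sided 0.05 test with 80 % power unadjusted then has

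power = Φ[(0.8416 + 1.96)/√(1 − ρ²) − 1.96].

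| ρ | 1 − ρ² | 2.8016/√(1 − ρ²) | Power |
|---|---|---|---|
| 0.2 | 0.96 | 2.859 | 81.6 % |
| 0.3 | 0.91 | 2.937 | 83.6 % |
| 0.4 | 0.84 | 3.057 | 86.4 % |
| 0.5 | 0.75 | 3.235 | 89.9 % |

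If the assumed correlation is instead with each single visit (r), averaging k visits with intraclass correlation ICC gives ρ² = r²/v, where v = [1 + (k − 1)ICC]/k. With k = 10 and ICC = 0.5 (both assumed), v = 0.55, and r = 0.3 corresponds to ρ = 0.3/√0.55 = 0.405, or about 86 % power. The two scales agree; they must only not be confused.

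**Mixing.** Suppose a SNP shifts the week-0 score by d = 0.3 SD and has no further effect under lithium. The unadjusted model carries r × d into the SNP effect. With 700 patients, a carrier share of 0.51 (allele frequency 0.30, dominant), k = 10 and ICC = 0.5:

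SE = √[0.55/(700 × 0.51 × 0.49)] = 0.0561.

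- r = 0.2: carried 0.06, z = 1.07, declared associated in 19 % of analyses.
- r = 0.3: carried 0.09, z = 1.60, 36 %.
- r = 0.5: carried 0.15, z = 2.67, 76 % (this r equals ρ = 0.67, well above the range in the table).

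A simulation with 6 visits and 300 replicates gave 15, 37 and 81 % unadjusted, against 4 to 6 % with the week-0 score as a covariate. The 0.3 SD shift is illustrative; the documents contain no such figure.

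**Would the existing checks catch it?**

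- *Episode frequency:* not if the SNP acts on severity and leaves frequency alone.
- *Depakote arm:* a severity SNP should also show there, so this helps. But the arm holds only patients who could not tolerate or failed lithium (Valproate crossover), and absence of association in that subset is itself read as support for lithium specificity.
- *SNP-by-time:* exploratory, and it does not change the main test of mean differences.

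**The case against.** The strongest reply has four parts.

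**Genotype precedes the week-0 score**, so this is not ordinary confounding. Adjusting changes the question to the SNP effect given starting severity, and for patients already on lithium the first score may already contain the response being sought. This stands. It argues for showing the adjusted model beside the unadjusted one, not for leaving it out.

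**The correlation may be low.** Follow-up starts after stabilisation to low CGI scores, and the same-scale score at entry partly reflects whether the patient came in depressed or manic. This also stands. A reader might take the gain of about 10 points at ρ = 0.5 as the expected loss; the documents do not support that, and at ρ = 0.2 the gain is 1.6 points. Nor does the whole spread of starting severity sit in the error term: only the share ρ² of follow-up variance does.

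**A week-0 score may not exist for all.** Table 2 puts week 0 under Stabilization, while patients already on lithium monotherapy go straight to the Observation Phase. A reader might infer from the table that everyone has a comparable baseline; that is not shown.

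**This is a secondary analysis in a condensed article**, with checks on natural course already planned. The secondary status is conceded. But the article does not leave the covariates open: it lists them, and it states how a persisting association will be interpreted.

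**Conclusion.** The point holds as a limited one about the secondary symptom-score models. Their stated covariates include neither starting severity nor entry route, and the first lithium-specificity check cannot tell a severity SNP from a lithium-response SNP when episode frequency is unaffected. The other planned checks reduce that risk but do not remove it.

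The precision cost is about 2 to 10 percentage points of power for assumed ρ of 0.2 to 0.5, from an assumed 80 %, with the lower end plausible. The mixing rates show that the mechanism can matter; they do not estimate how often it will occur, because they also rest on assumed values of d, r, ICC and number of visits. A reader might infer that the study's main lithium-response result is compromised. It is not: that result comes from the Cox relapse analysis, which this point does not touch.

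**What to change.** In the repeated-measures paragraph of the Statistics section:

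1. Add the entry-on-lithium indicator already offered for the Cox model.
2. Add the first available score on the same scale as the outcome (week 0 where taken), and let its slope differ by entry route.
3. Report each SNP model with and without the baseline score.
4. Call an association lithium-specific only if it persists in the baseline-adjusted model as well as after adjusting for episode frequency.

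This costs analysis-plan wording and no new assessments where week-0 scores are taken; for patients entering observation directly, the plan should say which score serves. The downside is small. The adjusted effect is conditional on starting severity, measurement error in that score leaves some mixing, and for patients already on lithium the score is not a pre-lithium value. The adjusted model is therefore most informative in patients who start lithium within the study, and the text should say so.

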## Methods and design

This study is an 11-site prospective, non-randomized open trial of lithium designed to ascertain a cohort of subjects with bipolar I disorder who experience protocol-defined relapse prevention as a result of treatment with lithium monotherapy. Prior to entry into the 1-month Observation Lithium Monotherapy Phase, three routes of entry will be permitted.Lithium Naïve Patients (LNP): LNPs will enter a 3-month Open Stabilization Phase designed to prospectively demonstrate response to lithium either as a component of Treatment As Usual (TAU) or monotherapy before entry into the 1-month Observation Lithium Monotherapy Phase. LNPs will enter the 1-month Observation Lithium Monotherapy Phase if and when they exhibit a score of 1 (normal, not ill) or 2 (minimally ill) on the Clinical Global Impressions of Severity Scale for Bipolar Disorder (CGI-S-BP Overall Bipolar Illness).Currently Lithium-treated Patients (CLTP): CLTPs on lithium monotherapy will enter the 1-month Observation Lithium Monotherapy Phase when they exhibit a score of 1, 2 or 3 on the CGI-S-BP Overall. For CLTPs as a component of TAU, they will spend up to 3 months during the Open Stabilization Phase slowly weaning off all other psychotropic medications. Once lithium monotherapy is achieved and a score of 1, 2 or 3 on the CBI-S-BP Overall is observed, they will immediately enter the 1-month Observation Lithium Monotherapy Phase.Inadequate Past Lithium-treated Patients (IPLT): IPLTs currently not taking lithium but believed to have had an inadequate past trial of lithium, either due to inadequate dose, blood level, duration, or adherence to treatment, will enter the 3-month Open Stabilization Phase to prospectively demonstrate response to an adequate trial of lithium (either as a component of TAU or monotherapy). IPLTs will enter the 1-month Observation Lithium Monotherapy Phase if and when they exhibit a score of 1 (normal, not ill) or 2 (minimally ill) on the CGI-S-BP.

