### Clinical course

Data will be collected on course of illness prior to randomization, including age of onset for bipolar disorder, number of prior episodes, past treatment response, childhood abuse (emotional, physical, sexual), medical conditions, psychoactive substance use, family history, prior lithium treatment and prior suicide attempt history, including lethality. Specifically, a history of episodes in the previous 2 years will be taken using a life chart method. This will be used as a covariate to correct for natural course in the statistical analysis.

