During the study development, the following factors were considered:Prospective vs retrospective. Almost all previous studies of lithium response have been done using standardized chart review and retrospective response data, which has the advantage of surveying the subject’s entire lifetime experience on lithium. However, it suffers the serious disadvantages of poor recall, state-related recall, lack of monotherapy (in general), qualitative instead of quantitative data and lack of observer ratings. For these reasons, we chose a prospective design. Though the much greater effort and expense will only allow for smaller sample sizes, we deemed the accuracy and superiority of the data to be the more important factors. This sample may serve as a “gold standard” sample for future studies, especially for replication of results.How many mood stabilizers to study? We considered a design where subjects would be randomized between lithium and two other mood stabilizers such as lamotrigine or valproate. Though this design would have given us invaluable comparative information, we chose instead to have a larger sample size and better statistical power for one drug, lithium. The crossover of lithium failures to valproate provides some opportunity for comparison.How to distinguish gene effects from natural course? If a genetic variant shows association to response, how do we know that this reflects the subject’s response to lithium vs. simply the natural course of the illness? Specifically, how do we know that a SNP is associated to lithium response or simply rapid cycling and is unrelated to drug? The scientifically ideal design would be to include a placebo arm as a control for natural course. However, given the severity of bipolar disorder, we deemed it neither ethical nor feasible to include such an arm. Instead, we have employed a detailed collection of information about lifetime cycling to covary for this effect. Of note, in the Perlis et al. study of lithium response in the STEP-BD sample, a similar inclusion of rapid cycling as a covariate had no effect on the results [42].Monotherapy. Though perhaps a therapeutic ideal, monotherapy using any drug is not usually achieved in the management of bipolar disorder. However, if we allowed multiple drugs, then we would remain unclear as to which drug was driving the response and to which drug a genetic variant is associated. For these reasons, we chose to require monotherapy, though it excludes partial responders and the generalizability.Acute vs prophylactic response. A shorter and faster study might have focused on the acute response to lithium in treatment of depression, mania or mixed states. However, the most widely used application for lithium is prophylaxis, and by studying relapse prevention we focus on the greatest clinical utility. Most patients also enter the study on other medications and the acute stabilization period is confounded by these other medications and the changes in medications during this periodDuration of follow up. Twenty-four months of follow up was selected because the STEP-BD study showed that, at 2 years, about 50 % of treated bipolar I patients had relapsed. Two years was therefore selected to maximize power.

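### The specificity rule is unreliable: persistence after adjusting for a two-year episode count does not show lithium specificity, and attenuation can be misread when many patients enter on lithium

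*Protocol article*

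**What the plan says.** The Statistics section of the protocol article gives two strategies for deciding whether a SNP effect is specific to lithium. The first examines whether "the inclusion of a covariate describing prior disease episode frequency affects the estimated association between SNPs and clinical relapse and/or symptom differences". Two conclusions are attached. One is "If the estimated association is mitigated, this will suggest that the SNPs are associated with the natural course of disease in general". The other is "If, however, the estimated association persists, this will suggest that the association is specific to lithium responsiveness". No size of change is given that would divide the two. The second strategy tests the same SNPs in patients crossed over to valproate and takes absence of association as support for specificity.

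The Clinical course section defines the covariate: "a history of episodes in the previous 2 years will be taken using a life chart method", followed by "This will be used as a covariate to correct for natural course in the statistical analysis". Time on lithium is not excluded. The Discussion describes it differently: "we have employed a detailed collection of information about lifetime cycling to covary for this effect". It presents this as the substitute for a placebo arm, which was judged unethical and infeasible.

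Patients already taking lithium are admitted: "CLTPs on lithium monotherapy will enter the 1-month Observation Lithium Monotherapy Phase" once their severity score permits. Under Participants, they are also excused from the requirement of an episode in the past 12 months if they have had none in the past 6. Statistics allows an indicator for having entered on lithium, and a test of whether associations differ by it, but ties neither to the specificity rule.

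**The concern.** The rule can go wrong in two directions.

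(a) A two-year count measures underlying cycling with error. Adjusting for an error-prone confounder removes only part of the confounding, so a SNP that influences only the natural course still shows an association, which the rule calls lithium-specific. Because every patient receives lithium, persistence also cannot exclude any other prognostic pathway.

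(b) For a patient who spent part of the window on lithium, episodes in that part are partly an earlier reading of the trial's own outcome. Adjusting for them can take out real lithium effect, and the rule then calls the SNP a natural-course marker.

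At stake is the label given to an associated SNP. That label matters because lithium-specific response is what the study sets out to find.

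**Working it through.** **The plan's own figure.** The article gives none for the specificity rule. The nearest is about 80 % power for a hazard ratio of 1.4 with 700 subjects (caption of Fig. 3), which is not disputed. Under a dominant model at minor allele frequency 0.30:
- Carriers are 1 − 0.7² = 0.51, with relapse risk 1 − 0.5^1.4 = 0.621.
- Expected events are 700 × (0.51 × 0.621 + 0.49 × 0.5) ≈ 393.
- √(393 × 0.51 × 0.49) × ln 1.4 − 1.96 ≈ 1.38, a two-sided power of 92 %.

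The same Schoenfeld formula reaches 80 % at an allele frequency of about 0.13. The stated figure is attainable but cannot be checked without the figure's allele frequencies.

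**Inputs from the article.** N = 700, two years of follow-up, hazard ratio 1.4, log-additive SNP coding, about half of patients relapsing (53 % in the simulation), and a two-year prior count.

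**Assumptions not in the article.** Minor allele frequency 0.30; prior episode rate r = 0.7 per year (varied from 0.35 to 3); share of patients already on lithium 0 to 100 %; those patients on lithium for the whole window; lithium halving the average rate; the standard deviations below.

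**Model.**
- Natural course: u = b_nat·G + noise (SD 0.8), where G is the centred allele count.
- Lithium effect: w = b_li·G + noise (SD 0.5).
- Relapse hazard on study: 0.5·exp(u + w) per year.
- Prior count: Poisson with mean 2r·exp(u) off lithium, and 2r·exp(u)·0.5·exp(w) on lithium.
- Cox model for G with and without log(count + 0.5). The already-on-lithium indicator is in both models at mixed shares.
- Retained share = adjusted log HR ÷ unadjusted log HR, from 3 × 40,000 subjects. The proportion still significant comes from 200 trials of 700, among those significant before adjustment.

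A natural-course SNP has b_nat = ln 1.4 and b_li = 0; a lithium SNP has the reverse.

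**Results at 0.7 episodes per year.**

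| Share on lithium at entry | Natural-course SNP: log HR before → after | Retained | Still significant | Lithium SNP: log HR before → after | Retained | Still significant |
|---|---|---|---|---|---|---|
| 0 % | 0.257 → 0.157 | 61 % | 47 % | 0.262 → 0.278 | 106 % | 98 % |
| 25 % | 0.256 → 0.156 | 61 % | 57 % | 0.253 → 0.248 | 98 % | 98 % |
| 50 % | 0.272 → 0.177 | 65 % | 68 % | 0.264 → 0.232 | 88 % | 90 % |
| 100 % | 0.263 → 0.177 | 67 % | 67 % | 0.258 → 0.177 | 69 % | 63 % |

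The 106 % is the usual rise in a Cox coefficient when a prognostic covariate is added.

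**Cause of (a).** With the true underlying rate u as covariate instead of the count, the natural-course SNP falls to about zero (log HR −0.005 to 0.014 over all runs). The residual association therefore comes from the imperfect proxy.

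**Sensitivity to the episode rate.**
- Natural-course SNP, 25 % share: 74 % retained at 0.35 per year, 45 % at 1.5, 31 % at 3.
- Lithium SNP, 50 % share: 94 %, 82 % and 77 % at the same rates.
- Lithium SNP, 100 % share: 79 %, 50 % and 37 %.

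**Effect of an off-lithium count.** This corresponds to the 0 % row. The lithium SNP keeps its effect, so (b) disappears. The natural-course SNP still keeps 61 %, so (a) remains. Redefining the window repairs one direction only.

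**The case against.** The strongest reply is that the rule carries information. The article asks whether the estimate is mitigated, not whether it stays significant. Measured on that one scale, a natural-course SNP loses 33–39 % of its log HR at 0.7 episodes per year, while a lithium SNP loses nothing to 12 % at shares up to 50 %. The two become indistinguishable only near a 100 % share. This stands: a reader might infer that the rule cannot separate the two mechanisms at all, and the calculations do not support that.

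A reader might also infer that, for patients entering on lithium, the count simply is lithium response. The documents do not support that either. They state neither how many such patients there will be nor how long they have taken lithium, and nothing requires two years. Only the on-lithium part of the window is affected.

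Third, the article already offers the already-on-lithium indicator and a test of differing associations. That test could expose direction (b). However, it is optional and unconnected to the specificity step, and the indicator as a main effect left both errors in place in the simulation.

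Fourth, the conclusions are worded as suggestions and backed by a valproate check. The check does not rescue them. It reads non-association as confirmation, in a group that failed or could not tolerate lithium (Valproate crossover section).

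**Conclusion.** The concern holds in limited form. Persistence after adjustment is weak evidence of lithium specificity whatever the share entering on lithium: a pure natural-course SNP keeps about 61–67 % of its log HR at 0.7 episodes per year, and 31–74 % between 3 and 0.35 per year at a 25 % share. Misreading a true lithium effect as natural course is negligible at a 25 % share (98 % retained) and material from about half upward (88 % at 50 %, 69 % at 100 %).

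The directions follow from the design. The sizes rest on the assumed episode rate, variances and lithium effect, and for the second error on the whole window being spent on lithium, which overstates it if exposure was shorter.

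It would be a further overreading to conclude that the main genetic analysis is compromised. The test of SNP against relapse does not use this rule; only the later interpretation does. The point is worth correcting but is not a must-fix.

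**What to change.** 1. Reconcile the two descriptions of the covariate: previous two years (Clinical course) and lifetime cycling (Discussion). A lifetime count would also contain time on lithium unless that is excluded.
2. Define the covariate as episode rate over time off lithium. For patients on lithium at entry, use the history before lithium, since lifetime course and prior lithium treatment are already collected. Keep the two-year version as a sensitivity analysis.
3. Make the already-on-lithium indicator and its test of differing associations part of the specificity step, and add the result in patients not on lithium at entry.
4. Replace the two conclusions with the SNP hazard ratio with and without the covariate and a confidence interval for the change, labelled supportive only. This is needed as well as item 2, which leaves direction (a) untouched.
5. Compare the SNP effects under lithium and valproate by estimate and confidence interval instead of reading non-significance as specificity. State that the valproate group contains only patients who failed or could not tolerate lithium.

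The cost is a covariate definition and analysis wording, with no new data collection. The downsides are older and less precise recall for patients already on lithium, and a weaker specificity claim. Time off lithium is also not untreated time, because the Discussion notes that most patients enter on other medications; that limit should be stated.
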